### Data collection, management, and statistical analysis

2.4.

Both evaluators (physiotherapist and neuropsychologist) will be responsible for exporting and filling in a database with variables from the scales and tests mentioned in Table 2 according to the code assigned to each patient to ensure his or her anonymity. To protect confidentiality during the study, the personal information of participants will be located separately from the main dataset on a local computer. The raw dataset will be maintained for 10 years after the completion of the trial with indefinite restricted access due to sensitive data. After the publication of the results trial, a fully anonymized patient-level dataset will be made publicly available on the registration trial website (clinicaltrials.gov). For participation in this study, no participant will receive any kind of incentives or compensation.

All analyses will be evaluated by intention-to-treat principles in terms of assignment to treatment and used a level of significance of 0.05. There are no interim analyses planned for this study. We will use the statistical software SPSS Statistics version 24.0 (IBM Corporation) for all the statistical analyses. Categorical variables were presented using frequency and percentage, and continuous variables as mean with standard deviation if they follow a normal distribution. To test for possible carryover effects of the experimental group, the sum of the values measured in the two periods for each subject will be calculated and compared across the two randomized groups (EG and PCG) using a test for independent samples (Serrao et al., 2019). There should be no difference if there is no sequence (balanceHOME program—usual daily activity or usual daily activity—balanceHOME program) effect.

To answer to the main aim of the study, a two-factor mixed multivariate analysis of variance (MANOVA) test was conducted to analyze the effects of within-subject factors (assessment times) and the between-subject factor (group) on the outcomes registered. The Bonferroni adjustment was used for *post-hoc* comparisons, and differences were declared statistically significant if the value of *p* was less than 0.05. Differences between groups for demographic outcomes were verified with a univariate analysis of variance (ANOVA) between-subjects test. Furthermore, to test for sex differences between groups, a chi-square analysis was used (San Martín Valenzuela et al., 2020b).

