#### Setting and eligibility criteria

2.2.1.

The recruitment of participants, the eligibility criteria assessment, obtaining informed consent (Supplementary material 3), and the intervention of the ACG will be carried out in the facilities of the neurorehabilitation center participant in the study. On the other hand, the pre-intervention, post-intervention, and 8-week follow-up evaluations will be carried out at the University of Valencia, while the interventions of the EG will be carried out at each participant’s home.

The recruitment and eligibility criteria assessments will be carried out by two different physiotherapists, who will verify the following inclusion criteria: (i) idiopathic PD; (ii) Hoehn & Yahr stage I-IV; (iii) independent gait with or without technical assistance; and (iv) stable parkinsonian medication for at least a month before the study star. On the contrary, the exclusion criteria will be as follows: (i) comorbidities that affect balance or walking; (ii) other neurological pathologies besides PD; (iii) chronic diseases not medically controlled; and (iv) participation in another physiotherapy program or sport activity during the intervention period or in the month before starting the study. Patient enrolment was started in August 2021 and is expected to be completed in August 2023. All patients are expected to have completed baseline testing in September 2023.

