#### Outcomes and participant timeline

2.2.3.

First, during the enrolment assessment, a standardized neurological clinical interview for Parkinson’s Disease (Supplementary material 4) will be performed. This interview includes questions related to habits, disease start, education, and working life. At the same time, weight, height, and body mass index will be measured with a wall stadiometer and a TANITA SC-240MA scale. The length of the lower limbs will also be measured during standing position with a tape measure from the anterior superior iliac spine and the medial malleolus. Asymmetries between the lower extremities greater than 1 cm will be considered within the first exclusion criteria (comorbidities that affect balance or gait). As mentioned above, each phase of the study has three evaluation moments: baseline (T0), post-8-week-training (T1), and follow-up (T2) at 8 weeks after the physiotherapy programs have finished. Assessments will be performed by a different physiotherapist from recruitment and treatment besides a neuropsychologist, both blinded to the treatment assignment. The participants will be evaluated in an ON-medication state (1 h after the dopaminergic dose) on the schedule described in Figure 1. In each measurement session, the severity of the disease (Hoehn and Yahr, 1967; Fahn et al., 1987), cognitive and mental status (Hamilton, 1959, 1960; Mahieux et al., 1995; Dubois et al., 2000; Marinus et al., 2003), perception on quality of life (Peto et al., 1995; Powell and Myers, 1995; Sandín et al., 2020), and balance and gait performance will be registered through clinical tests (Tinetti, 1986; Giladi et al., 2000; Kegelmeyer et al., 2007; Franchignoni et al., 2010) as well biomechanics instruments. Table 2 shows the scales and clinical tests that will be used to evaluate the participants. For balance biomechanics, assessment will be used a dynamometric platform (Dinascan/IBV Biomechanics Institute of Valencia, Valencia, Spain) and the NedSVE®/IBV software (version 5.3.0.1, Biomechanics Institute of Valencia, Valencia, Spain). Balance will be assessed through the Romberg tests under four static conditions with increasing difficulty (see Figures 2A,B): (i) eyes open; (ii) eyes closed; (iii) eyes open on a foam rubber; and (iv) eyes closed eyes on the foam rubber (thickness of 9 cm, 56.7 kg/m3 of density, and resistance of 25%) (Escamilla-Martínez et al., 2021). Participants were asked to find the most stable position while barefoot with their arms relaxed on either side of the body, with their heels together and toes apart at a 30° angle. Additionally, four static functional balance tests will be assessed, using the Romberg test protocol with their eyes open: (i) to see the time on an analogy clock (visual); (ii) to answer a simple question (verbal); (iii) to pour the contents of one glass into another (lower motor); and (iv) to simulate comb the hair (upper motor). The instructions for each task were standardized to ensure uniform execution of the gesture. Participants will be asked to remain as still as possible with their heads in a neutral position and their gaze forward, except for the lower motor test where they will be allowed to observe their hands. Each test will last for 30 s and will be recorded two times. Finally, dynamic balance will be assessed with stability limits and rhythmic weight shift tests on the platform (Balaguer García et al., 2012). In the stability limits test, participants from the Romberg position will have to move a cursor (which reflected the position of their CoP) toward eight targets (front, front-right, right, rear-right, rear, rear-left, left, and front left) visualized on a computer monitor placed in front at their eye level. Once the target is reached, the subject will have to maintain the posture with the CoP displaced at the limit of stability until the end of the 8 s of each test (Balaguer García et al., 2012). On the other hand, in the rhythmic weight shifts tests, subjects will have to move their CoP to the direction and velocity of a moving target visualized on the computer monitor (Balaguer García et al., 2012). Each dynamic test will be registered two times. As a result, the primary outcome of the study will be the CoP sway area, which is defined as the surface over which the CoP moves during the measurement and is a valid indicator of detecting postural control changes in dual-task conditions (Campolettano et al., 2020; Morenilla et al., 2020). The secondary outcomes are shown in Table 2 and consist of biomechanics and clinical variables related to static and dynamic balance.

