#### Sample size and recruitment

2.2.4.

The software G*Power v.3.1 (Faul et al., 2007) has been used to determine the necessary sample size to detect a change in the primary outcome CoP sway area and differences between the groups (EG, PCG, ACG), with a small-medium effect (*f* = 0.15), a statistical significance of 5% at the two-tailed level, and a power of 95%. As a result of the above, 93 people diagnosed with PD will be recruited. If 20% of possible dropouts are also considered during the study, the initial recruitment should be 112 people. The sampling process will consist in the consecutive non-probabilistic method, in which the selection of individuals is carried out based on the fulfillment of participation criteria. The recruitment of participants began on 1 July 2021 and we estimate its completion on 31 July 2023. The participant recruitment procedure consists of three steps. First, the neurorehabilitation center has selected the possible candidates for the study based on personal and clinical characteristics, asks them by email the authorization to send information about the study, and contacted them using their telephone number. Then, the principal investigators called potential candidates to resolve possible doubts and confirm their participation. Finally, a physiotherapist will assess the selection criteria for all the volunteers and will provide informed consent for their signatures. The recruitment process will be repeated to complete the number of participants estimated for the study, extending participation to a new clinical center or public hospital if necessary.

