### Monitoring

2.5.

No external professionals will be contact for data monitoring procedures. Rather, internal data monitoring is coordinated by a Data Monitoring Committee. For this purpose, one member of each institution of the study integrates the Committee. The monitoring will be independent of the evaluation appointments of this study and will be carried out by telephone monthly to all participants to record the following: (1) changes on Parkinsonian or other medication, (2) falls/week or other adverse events, (3) changes on other therapies (psychology or speech therapy) and neurology appointments, and (4) changes in physical activity outside the study. The Data Monitoring Committee will decide whether trial participation should be discontinued based on the reports from monitoring. The monitoring data will be anonymized and published once the study is over on the trial registration website (clinicaltrials.gov).

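### Intention-to-treat is stated for all analyses, but the named mixed MANOVA, run as written, analyses only participants with complete records

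*Protocol article*

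**What the plan says.** Section 2.4 commits to one principle for every analysis: "All analyses will be evaluated by intention-to-treat principles in terms of assignment to treatment". For the main aim it then names "a two-factor mixed multivariate analysis of variance (MANOVA) test was conducted to analyze the effects of within-subject factors (assessment times"), with group as the between-subject factor and the registered outcomes as dependent variables. On software: "We will use the statistical software SPSS Statistics version 24.0 (IBM Corporation) for all the statistical analyses". The carryover test in the same section is also a within-person calculation: "the sum of the values measured in the two periods for each subject will be calculated". The article mentions no imputation.

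Section 2.2.3 sets the visits: "each phase of the study has three evaluation moments: baseline (T0), post-8-week-training (T1), and follow-up (T2"). Section 2.2.4 requires 93 people and allows for loss: "If 20% of possible dropouts are also considered during the study", initial recruitment is to be 112.

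Two other statements bear on who stays in the trial. Section 2.2.1 lists as exclusion criterion (iv) "participation in another physiotherapy program or sport activity during the intervention period or in the month before starting the study". Section 2.5 provides that "The Data Monitoring Committee will decide whether trial participation should be discontinued based on the reports from monitoring"; those reports are monthly telephone records of medication changes, falls and other adverse events, other therapies and outside physical activity.

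Only the experimental group (EG) and the passive control group (PCG) are randomised, 1:1 (section 2.3). The active control group (ACG), the other third, is not.

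**The concern.** Intention-to-treat has two parts: people are analysed in the group to which they were assigned, and everyone randomised is analysed. A mixed MANOVA in SPSS meets the first but, used alone, not the second. It needs a full row per participant, so one missing visit, or one missing outcome among those modelled together, removes the person and all their other data. The carryover test likewise needs data from both periods.

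At stake is the comparison that randomisation protects. Participants know their allocation, one arm trains while the other waits, and the outcome is balance in a progressive disease. If those who leave differ from those who stay, and differ in another way between arms, the contrast among completers no longer estimates the effect in the people randomised. A report could still carry the intention-to-treat label.

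**Working it through.** **1. The plan's sample size.** Inputs from section 2.2.4: f = 0.15, alpha 0.05, power 95%, three groups. The number of assessments m, the correlation rho and sphericity are not given and are assumed here. For the within-between interaction in a repeated-measures ANOVA, lambda = f² × N × m / (1 − rho), df1 = (k − 1)(m − 1), df2 = (N − k)(m − 1).

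- k = 3, m = 6, rho = 0.5, N = 93: lambda = 0.0225 × 93 × 6 / 0.5 = 25.11, df 10 and 450, power 0.952. This reproduces 93.
- k = 3, m = 3, rho = 0.5, N = 93: lambda = 12.56, df 4 and 180, power 0.811. With m = 3, 93 gives 95% power only if rho is about 0.68.
- Dropout: 93 × 1.20 = 111.6, so 112. This reproduces the plan's figure.

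**2. Who remains if the 20% are dropped.**

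| | Recruited | After 20% loss | Share of the required 93 |
|---|---|---|---|
| All three groups | 112 | 112 × 0.80 = 89.6, about 89 | 93 |
| EG and PCG (two-thirds) | 74.7, about 75 | 74.7 × 0.80 = 59.7, about 60 | 62 |
| Each sequence | 37.3, about 37 | 37.3 × 0.80 = 29.9, about 30 | 31 |

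The overall figure includes the non-randomised ACG. The intention-to-treat question concerns the second and third rows.

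**3. Effect on power.** At N = 89, power is 0.941 instead of 0.952 (m = 6, rho = 0.5), or 0.791 instead of 0.811 (m = 3, rho = 0.5). The shortfall against 93 arises because 93 was multiplied by 1.2; dividing gives 93 / 0.80 = 116.25, so 117. That is a separate and minor matter.

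**4. Intermittent missing visits.** The 20% may not include people who miss a single visit. If visits are missed independently with probability q (an assumption), the share with complete records is (1 − q)^v for v visits.

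| q | 3 visits | 6 visits |
|---|---|---|
| 5% | 85.7%, about 64 of 75 | 73.5%, about 55 of 75 |
| 10% | 72.9%, about 55 of 75 | 53.1%, about 40 of 75 |

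The six-visit column applies only if both crossover phases enter one model. The article does not say so, and the ACG has no second phase.

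**5. Bias.** Dropping a fraction p of an arm shifts its mean change by p × (mean change in completers − mean change in those dropped). With p = 0.20 in both arms, the contrast shifts by 0.20 × (difference of that quantity between arms). If the difference is zero, so is the shift; at an assumed 0.5 SD it is 0.10 SD. The article gives nothing from which to choose a value.

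**6. The other two statements.** Criterion (iv) has one limb for the month before entry and one for the intervention period. Randomisation follows T0 (section 2.1), so actual participation under the second limb can occur only after allocation. The committee's power in section 2.5 is over trial participation as a whole, and the article does not say whether T1 and T2 assessments continue afterwards.

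**The case against.** The strongest reply is that no complete-case rule is written. Listwise deletion is a property of the named procedure; data could be imputed first, and such detail commonly sits in a statistical analysis plan or full protocol not shown here. The intention-to-treat sentence is also limited to assignment, which can be read as grouping by allocation only. This stands in part: a complete-case analysis is a consequence of running the method as written and not a stated intention. It does not remove the point, because the article itself fixes a method that discards incomplete records beside an intention-to-treat claim for all analyses. Keeping completers under their assigned label does not analyse everyone randomised.

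The 20% allowance does not prove that a completers' analysis is intended either, since such inflation is routine under any method. It is used here only to size the loss.

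A reader might go further and infer that criterion (iv) and the committee rule delete randomised people from the analysis. The article does not support that. Criterion (iv) is among the criteria verified at recruitment, Table 2 marks the eligibility screen at enrolment only, and the wording may be meant to screen out planned activity. Section 2.5 says nothing about deleting data. Nor does the article say that untreated controls seek more outside exercise; the promise of the home programme after T2 may discourage it. What stands is ambiguous wording that could be applied against the intention-to-treat statement.

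**Conclusion.** The concern holds for the analysis method. Run as written and without imputation, the main analysis covers people with complete records: at the plan's own dropout, about 60 of about 75 randomised participants, and about 89 of 112 overall against 93 required. This assumes that the 20% loss is spread evenly over groups and that every dropout lacks at least one modelled visit.

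The cost in power is modest. The case for change rests on the comparison being among completers, with a bias that cannot be sized from the article and is zero if dropout is unrelated to arm and outcome. Differential removal by arm is plausible but undocumented. The two participation rules need clarifying and are not shown to breach intention-to-treat. The ACG is outside this conclusion, because it was never randomised.

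**What to change.** - Define the analysis set for the randomised comparison as all EG and PCG participants, in their assigned sequence. State that comparisons with the ACG are non-randomised and outside the intention-to-treat claim.
- Analyse CoP sway area with a likelihood-based linear mixed model (time, group and their interaction, with within-person correlation) on every available visit. Multiple imputation before the MANOVA is the alternative if the MANOVA is kept.
- Add a sensitivity analysis for data not missing at random, for example shifting the unobserved outcomes by a range of amounts, separately by arm.
- Reconcile criterion (iv) with section 2.4: say whether it is checked at entry only, and that a randomised person who later takes up other activity stays in the analysis set. The monthly calls already record such activity.
- Reconcile section 2.5 with section 2.4: say that a randomised person whose participation is discontinued stays in the analysis set and, with consent, is still assessed at T1 and T2. The grounds on which the committee acts are not at issue here.

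The cost is a short amendment, slightly more analysis work and a few extra assessment visits. The mixed model relies on data being missing at random, which is why the sensitivity analysis is needed. Clarifying continued assessment is the urgent part, because visits not made cannot be recovered at the analysis stage.

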### Study design

2.1.

The balanceHOME trial is designed as a randomized, controlled, and blind evaluator trial with a crossover intervention group. To write this protocol was used as a guide the Standard Protocol Items for Randomized Trials (SPIRIT) guidelines (Chan et al., 2013) and the Consolidated Standards of Reporting Trials statement for randomized controlled trials (Moher et al., 2010). The SPIRIT guidelines can be consulted in Supplementary material 1. Once the study was designed, it was registered on ClinicalTrials.gov (NCT04963894) on 15 July 2021 with the approval information of the Human Research Ethics Committee of the Experimental Research Ethics Commission of the University of Valencia obtained (Supplementary material 2).

The balanceHOME will be started with a baseline assessment session (T0) and followed by random allocation to one of two study groups: the experimental group (EG) or the passive control group (PCG). Additionally, a third group of participants with PD who habitually developed a conventional group physiotherapy program (Active Control Group, ACG) will be included in the evaluation process. At the end of the interventions (8 weeks), a post-training evaluation (T1) will be carried out, and subsequently, a follow-up assessment (T2) 8 weeks after the physiotherapy programs have finished. At this point, patients from PCG will switch with EG to receive the functional balance home program. The EG will follow a 4-month washout period (Serrao et al., 2019) before continuing as passive control participants (see Figure 1). The crossover design allows to control the intra-individual changes (due to personal characteristics and disease presentation), offer all the research benefits to the participants, and maximize the sample size it can achieve.

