
Another relevant aspect is that this protocol aims to solve is the inclusion of dual tasks in the evaluation of balance. Biomechanical balance is usually evaluated as single-tasks on the dynamometric platform (Smania et al., 2010; Kara et al., 2012; Santos et al., 2017; Soke et al., 2019). Complementing the static balance test with dual tasks would provide results of balance performance in real-world situations. Previously, the impact of dual tasks on the gait of trained and untrained people with PD has been determined, finding that verbal secondary tasks have a greater impact on motor performance than visual or motor secondary tasks with the arms (San Martín Valenzuela et al., 2020a,b). In this way, the balanceHOME protocol pretends to resolve methodological issues and research questions relevant to the advancement of physical rehabilitation of balance in the population with Parkinson’s disease.

This protocol will make it possible to facilitate highly challenging functional balance exercises for people with PD at their homes, using common materials of daily use. Similarly, the objective assessment methodology and the balanceHOME protocol will allow us to identify small changes in the balance performance of people with different stages of disease severity and to determine the effectiveness of the home program in people without and with cognitive impairment, which has not been done until now as we will be able to establish the scope that physiotherapy has when it is applied in patients with motor and cognitive failures. Unlike the authors who report improvements below 50% in objective parameters, we think that the structured and progressive dynamics of balanceHOME program can exceed these values of improvement in both dynamic and static balance in single and dual conditions, while performing secondary cognitive and motor tasks of the arms during standing balance maintenance. Furthermore, due to the convenience of home rehabilitation, we think that the effects may achieve better retention during the follow-up period than standard control therapy. This protocol aims to promote change in functional balance physiotherapy both in evaluation and rehabilitation, bringing day-to-day conditions closer to clinical practice.

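### The carryover test on period sums has roughly 9–11% power for a carryover as large as the planned effect, and unequal second-phase timing stops it from isolating carryover

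*Protocol article*

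**What the plan says.** Section 2.4 (Data collection, management, and statistical analysis) describes the carryover check: "the sum of the values measured in the two periods for each subject will be calculated and compared across the two randomized groups", using a test for independent samples. Its one sentence on interpretation is "There should be no difference if there is no sequence" effect. All analyses "used a level of significance of 0.05". The section gives no power, margin or decision rule for this check.

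Section 2.1 (Study design) sets the timing. Training lasts 8 weeks, T2 follows 8 weeks after the programmes end, and PCG then switches to the home programme. For the other sequence, "The EG will follow a 4-month washout period" before its passive-control period. The same section says the crossover is meant to maximise the attainable sample size.

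The Discussion adds, on the home programme, that "we think that the effects may achieve better retention during the follow-up period than standard control therapy".

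**The concern.** Two features weaken the check. First, each person's sum is compared with other people's sums, so the full between-person variance enters. A crossover is sized on within-person information, and a between-person test inside it will usually see only very large carryover. Second, the rule that sums should agree when there is no sequence effect presumes that both sequences meet the second period at the same point in time. Here they do not, and the Introduction describes Parkinson's disease as progressive.

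At stake is the use of second-phase data. If some training benefit is still present when EG acts as passive control, a simple two-period treatment estimate is biased, and the planned check would be unlikely to reveal it.

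**Working it through.** **Inputs from the protocol.** Section 2.2.4 gives f = 0.15, 5% two-sided, 95% power, "93 people diagnosed with PD will be recruited", and 112 after 20% dropout. The Abstract places two-thirds in the crossover, and section 2.3 randomises 1:1. This gives 93 × 2/3 / 2 = 31 per sequence, or 112 × 2/3 / 2 ≈ 37 with no dropout.

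**Assumptions of this check.** d = 2f = 0.30 for two equal groups, and a between-period correlation ρ of 0.5 to 0.8. The protocol states neither.

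**The protocol's own figure.** For a group-by-time interaction, the noncentrality is N·f²·m/(1−ρ). With 3 groups, m = 6 measurements and ρ = 0.5, it is 93 × 0.0225 × 6 / 0.5 = 25.11 on 10 and 450 df, giving 95.2% power (94.95% at N = 92). So 93 reproduces, and 93 × 1.2 = 111.6, rounded to 112. But m and ρ are unstated, and ACG does not cross over, so six measurements do not describe that group. With m = 3 the noncentrality is 12.56 on 4 and 180 df, power is 81%, and about 140 people would be needed.

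**What the sum estimates.** Let τ be the treatment effect, λ the carryover into EG's passive phase, and δ the difference between the sequences' second-period time effects. Then
- difference in mean sums (EG − PCG) = λ + δ;
- simple two-period treatment estimate = τ − (λ + δ)/2.

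Only when δ = 0 does the sum difference measure carryover.

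**Power of the test (δ = 0).** SD of a sum = σ√(2(1+ρ)); SE = that SD × √(2/n); power from the noncentral t. The last column is the smallest carryover detectable with 80% power.

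| n per sequence | ρ | SD of sum | SE | Power at 0.30 SD | Detectable at 80% |
|---|---|---|---|---|---|
| 31 | 0.5 | 1.73 | 0.440 | 10.3% | 1.25 SD |
| 31 | 0.7 | 1.84 | 0.468 | 9.7% | 1.33 SD |
| 31 | 0.8 | 1.90 | 0.482 | 9.4% | 1.37 SD |
| 37 | 0.5 | 1.73 | 0.403 | 11.4% | 1.14 SD |
| 37 | 0.7 | 1.84 | 0.429 | 10.6% | 1.22 SD |
| 37 | 0.8 | 1.90 | 0.441 | 10.3% | 1.25 SD |

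At 31 per sequence and ρ = 0.5, the 95% interval for the sum difference has half-width 2.00 × 0.440 = 0.88 SD, about three times the planned effect. For 80% power at 0.30 SD, 524 (ρ = 0.5) to 628 (ρ = 0.8) per sequence would be needed.

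**Sensitivity.** Converting f for a three-group spread gives d up to 0.37 and power of at most about 15%. Summing change scores instead of raw values, which the text does not say, gives about 13–30%.

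**Timing.** Four months ≈ 4 × 52/12 = 17.3 weeks. PCG starts its second phase at 8 + 8 = week 16. EG starts at 8 + 17.3 ≈ week 25 if the washout runs from the end of training, or 16 + 17.3 ≈ week 33 if it runs from T2. The gap is about 9 or 17 weeks, so δ need not be zero. The protocol gives no figure from which to size it.

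**First-phase comparison, for scale.** With 31 per arm and d = 0.30, power is 21% unadjusted. Adjusting for T0 divides the residual SD into d as 0.30/√(1−ρ²), giving 27% at ρ = 0.5 and 37% at ρ = 0.7.

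**The case against.** A reader might infer that the trial will take a non-significant result as proof of no carryover and pool the second phase on that basis. The text does not say so. It states only that sums should agree if there is no sequence effect, and it sets no gate. What follows from the test may sit in an analysis plan that is not shown. This limits the point to what the test can and cannot tell.

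A reader might also infer that the trial predicts carryover. The Discussion remark is hedged, compares with standard therapy, and concerns the follow-up period, which ends 8 weeks after training. It does not predict benefit beyond the 4-month washout. The washout is a genuine safeguard, and each phase has its own baseline. Both make serious bias less likely; neither makes the test informative.

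The bias formula applies to a simple two-period estimate. The stated main analysis is a time-by-group mixed MANOVA, and the protocol does not describe a pooled crossover estimate. Halving of a 0.30 SD effect to 0.15 SD is therefore a worst case: full persistence, that estimator, and δ = 0. Larger carryover is also less easily missed: at 31 per sequence and ρ = 0.5, power is 43% at 0.8 SD and 61% at 1.0 SD.

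Finally, Figure 1 is not available here and may settle when the washout begins. PCG switching at T2 and a washout for EG alone are stated in the text, so some gap remains under either count.

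**Conclusion.** The point stands in a limited form. The sum test has about 9–11% power for a carryover of 0.30 SD with 31 to 37 per sequence, given d = 2f and ρ from 0.5 to 0.8; other conversions of f raise this to at most about 15%. Non-significance would say almost nothing about a carryover of the planned effect's size. Separately, and without any power assumption, the unequal start of the second phase means that a difference in sums is not specific to carryover: time and progression can produce one or offset one.

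This does not show that carryover will occur, that the washout is inadequate, or that the crossover is invalid. It shows that the chosen check cannot give the reassurance for which such a check is normally run. The size of any timing effect on sway area cannot be derived from the protocol.

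**What to change.** 1. State that the sum test will not decide whether second-phase data are used.
2. Report the sequence estimate with its 95% confidence interval in place of a significance verdict, noting that it combines carryover with any timing difference.
3. Prespecify the randomised first-phase EG versus PCG comparison at T1 and T2, adjusted for T0, as a carryover-free analysis beside the two-phase analysis.
4. Fit the two-phase model with each phase's own baseline and actual weeks since randomisation.
5. State from which time point the 4-month washout is counted, so that the sequence timing can be read from the text.

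All of this uses assessments already scheduled; the cost is wording and some extra analysis. The real trade-off is precision. The first-phase comparison has only about 21–37% power at 0.30 SD with 31 per arm, so whether it should be the sole confirmatory analysis, or stand beside the two-phase result, is for the sponsor to decide and state in advance.
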